### **Investigation of a rising CEA during follow-up**

If a patient has a rising CEA during follow up, the following algorithm of investigation is recommended:

1. A CT chest/abdomen/pelvis should be the first-line investigation. The scan should be reviewed by an experienced GI radiologist (e.g. the study radiologist).
2. If no pelvic relapse is seen and no distal metastasis, particularly in the liver, then patients should proceed to an MRI pelvis and an MRI of the liver with liver specific contrast.
3. If no cause for the elevated CEA is found after MRIs, then a FDG-PET scan is recommended.

All imaging performed to investigate a rising CEA should be completed as per standard radiology guidelines,

### **Investigations for a suspected pelvic/distant relapse**

The pelvic/distant relapse should be discussed at an MDT and investigations, including imaging, and surgery if indicated, should be performed according to local practice. Patients with evidence of curative disease will continue to be followed up and information about further treatment captured on the **ANNUAL FOLLOW-UP Form**. If the disease is only considered amenable to palliative care then the patient should discontinue trial treatment and be followed up annually (by completion of the **ANNUAL FOLLOW-UP Form**) unless full consent for data collection is withdrawn. **Patients with evidence of suspected pelvic relapse must be treated at least as urgently as a primary rectal cancer by the surgical team.**

## **11.1 POST-SURGERY FOLLOW-UP**

Follow-up after surgery will include regular clinical follow-up as per usual practice. A CT scan should be carried out after surgery and following the completion of chemotherapy as per usual practice. It is recommended that CEA should be assessed every 6 months and thorax/abdominal/pelvis CT scans performed annually for the first 3 years, or as clinically indicated. The primary outcome of the main Phase III TRIGGER Trial compares the disease-free survival at 3 years from the start of chemoradiotherapy. A full investigation for recurrent disease (including CEA and a pelvis/thorax/abdomen CT scan, colonoscopy for metachronous disease) should be undertaken at this time point. The use of investigations after 3 years is left to clinical discretion but disease status for assessment of overall survival and disease free survival will

be collected at 5 years from the surgical clinics/GP patient records. The information routinely recorded in normal clinical notes should be sufficient for completion of the **ANNUAL FOLLOW-UP Form**.

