confirm the questionnaires arrived and to re-send if necessary. If there is no response send a second questionnaire 2 weeks later. If there is no response by 12 weeks (15 months from the end of CRT), we will accept that the patient preferred not to take part. If the patient has a disability that prohibits them from completing the forms by hand we recommend reading the questions out over the phone.

8. **Oncological outcomes** – 24 months and 36 months from the completion of CRT please complete the **ANNUAL FOLLOW-UP Form**.
9. **PROMs** - 36 months (not at 24 months) from the completion of CRT the patients will be asked to completed the same **QUALITY OF LIFE Form**.

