## 10. ASSESSMENT SCHEDULES

Please refer to the assessment schedules below for details of assessments to be performed, timelines and the CRFs to complete (further details relating to CRF completion can be found at the front of the CRF pack).

- Radiological assessment will be performed as per [Appendix 6](#) with synoptic reporting according to the allocated **POST-TREATMENT MRI FORM**.
- Chemotherapy toxicity will be assessed at the end of each cycle during treatment and residual toxicity assessed at the 12-month follow-up visit.
- When surgery is performed, surgical morbidity will be recorded intra-operatively and both early (6 weeks) and late (up to 12 months) surgical complications will be recorded post-operatively.
- **The QUALITY OF LIFE Form** will be completed by all patients at registration. For patients that undergo surgery the QoL forms should be completed again at 1 and 3 years following the completion of CRT. For patients who defer surgery the QoL forms should be completed at 1, 3 and 5 years from the time of CRT completion.
- Adverse events should be recorded from the date of the post-CRT MRI scan until 30 days after the patient's last dose of chemotherapy received during the intervention phase of the trial. Residual toxicity will be assessed at 12 months. Concurrent medications should be recorded at registration and updated from randomization until 30 days after the patient's last dose of chemotherapy. .
- **ANNUAL FOLLOW-UP Forms** should be completed at 12 months from the end of CRT and annually thereafter up to 3 years in those that undergo surgery and up to 5 years in those who defer surgery.

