### 11.2.1 SURVEILLANCE SCHEDULE FOR PATIENTS WHO DEFER SURGERY

| Time line from end of CRT     | Visit window | Clinic out-patient appointment b | Patient reported outcome measures c | Scans     | Endoscopy   | Completion of Case Report Forms d                                                                              |
|-------------------------------|--------------|---------------------------------------------|------------------------------------------------|-----------|-------------|---------------------------------------------------------------------------------------------------------------------------|
| 6 months ae        | ± 1 month    | X                                           |                                                | MRI       | Flex Sig    | 5B.INTERVENTION ARM POST-TREATMENT MRI
12. SURVEILLANCE                                                                |
| 9 months e         | ± 1 month    | X                                           |                                                | MRI       | Flex Sig    | 5B.INTERVENTION ARM POST-TREATMENT MRI
12. SURVEILLANCE                                                                |
| 1 year e           | ± 1 month    | X                                           | EORTC QLQ-C30, LARS, EQ-5D                     | MRI
CT | Colonoscopy | 5B.INTERVENTION ARM POST-TREATMENT MRI
10. TOXICITY
11. ANNUAL FOLLOW-UP
12. SURVEILLANCE
17. QUALITY OF LIFE |
| 1 year 3 months               | ± 1 month    | X                                           |                                                |           |             | 12. SURVEILLANCE                                                                                                          |
| 1 year 6 months e  | ± 1 month    | X                                           |                                                | MRI       | Flex Sig    | 5B.INTERVENTION ARM POST-TREATMENT MRI
12. SURVEILLANCE                                                                |
| 1 year 9 months               | ± 1 month    | X                                           |                                                |           |             | 12. SURVEILLANCE                                                                                                          |

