### 11.3 DEFINITIONS REQUIRED FOR FOLLOW-UP

**Complete response** is defined as undetectable disease at the site of the primary tumour following pre-operative chemotherapy and/or radiotherapy. A pre-fix to denote the mode of assessment must also be included - clinical (c), MRI (mr) and pathology (p).

**Disease recurrence** is defined as either evidence of loco-regional recurrence or established metastatic disease. The time to the event is measured from the start of chemoradiotherapy to the date of the diagnostic investigation or MDT.

**Regrowth** is defined as the first recorded evidence of disease at the site of the primary tumour, in a patient with previous investigations suggesting an apparent complete response or undetectable disease (mrTRG1&2). The terms 'early regrowth' and 'late regrowth' will not be used in the trial.

**Unsalvageable regrowth** is defined as a tumour with radiological evidence of a good response that is initially managed by deferral of surgery but progresses. The extent of progression means that pCRM involvement becomes inevitable and so surgery is not performed, or pCRM involvement occurs when surgery is attempted.

**Loco-regional recurrence** (one of):

- Clinical recurrence with biopsy proof of recurrence
- CEA elevation and enlarging or new mass (includes pelvic, nodal and peritoneal disease). Biopsy confirmation is contraindicated or not feasible
- CEA non-secretors: enlarging or new mass (includes pelvic, nodal and peritoneal disease). Biopsy confirmation is contraindicated or not feasible (with or without PET/CT confirmation)

**Distant Metastases** (one of):

- This is defined as any confirmed evidence of disease above the L5/S1 junction
- Clinical recurrence with biopsy proof of recurrence
- CEA elevation and evidence of distant metastases. Biopsy confirmation is contraindicated or not feasible

- CEA non-secretors: evidence of distant metastases. Biopsy confirmation is contraindicated or not feasible (with or without PET/CT confirmation). Initial report to Trials Unit should define this as SUSPECTED. A further report 6 months later should define this as CONFIRMED if supported by MDT review.

***Inoperable Disease*** (one of):

- MDT decision that the local extent of disease on the post CRT pelvic MRI is not resectable
- At laparotomy the local extent of disease is not resectable

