## **1.2 DOSE**

Phase I: 45Gy in 25 fractions in 5 weeks.

Phase II: 9Gy in 5 fractions in one week (consider 5.4Gy in 3 fractions if significant amounts of small intestine within the 95% isodose).

For VMAT/IMRT plans; simultaneous integrated boost will be considered in discussion with the trials team.

Gaps in patient's treatment should be avoided and when occur for clinical or nonclinical (breakdowns) conditions, the consultant clinical oncologist should be advised and local protocol followed.

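### The protocol runs 3-year DFS on conflicting clocks, so the deferral patients' 3-year scan falls nominally 5 to 6 weeks after the operated patients' check

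*Protocol*

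**What the plan says.** **Origin of DFS.** Section 3.1 says the amendment for the phase III trial will define DFS from registration, which takes place up to 4 weeks before CRT (7.1.1, 10.1). Section 11.1 says the phase III primary outcome "compares the disease-free survival at 3 years from the start of chemoradiotherapy". Section 11.3 says of disease recurrence: "The time to the event is measured from the start of chemoradiotherapy to the date of the diagnostic investigation or MDT".

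**Timing of the 3-year disease check.**
- Operated patients, investigation: having named the 3-year point from the start of CRT, 11.1 continues: "A full investigation for recurrent disease (including CEA and a pelvis/thorax/abdomen CT scan, colonoscopy for metachronous disease) should be undertaken at this time point". It gives no window.
- Operated patients, form: section 10 says of the yearly form that it "should be completed at 12 months from the end of CRT and annually thereafter up to 3 years in those that undergo surgery". Sections 8.1 and 8.3 and the schedules in 10.1 and 10.3 use the same anchor.
- Deferral patients: the 11.2.1 table is headed "Time line from end of CRT". Its 3-year visit has MRI, CT and flexible sigmoidoscopy with a window of ± 2 months. Its 2-year visit has MRI and CT. Its 2.5-year visit has clinical examination and CEA but no scan.

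**Use of the data.** Sections 4.5 and 11.1 word the phase III primary outcome as DFS at 3 years. Sections 3.1 and 14.2.2 carry feasibility patients into the phase III analysis.

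**The concern.** A recurrence found by imaging is dated to the investigation or the MDT, so the scan date decides on which side of a 3-year cut it falls. For operated patients the check is written to sit on the cut. For deferral patients it is written to fall after it. By plan, control patients go to surgery (8.1) and deferral is offered only within the intervention arm (8.2 and 8.3), so the stagger follows treatment arm and its direction is known: it favours intervention.

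The operated pathway also disagrees with itself, because its investigation and the form that records it run from different dates. Two sites could follow the protocol correctly and scan at different times.

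**Working it through.** **1. Length of CRT.** Appendix 3, section 1.2: "Phase I: 45Gy in 25 fractions in 5 weeks", then "Phase II: 9Gy in 5 fractions in one week", or 3 fractions for the smaller boost. That is 5 weeks without a boost and 6 with the full one. In months: 5 × 7/30.4375 = 1.15 and 6 × 7/30.4375 = 1.38.

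**2. Deferral 3-year scan, counted from the start of CRT.**
- Nominal: 36 + 1.15 = 37.1 months to 36 + 1.38 = 37.4 months.
- Window ± 2 months: 35.1 to 39.1 months (5 weeks), or 35.4 to 39.4 months (6 weeks).
- Share of the window after 36 months, if visits spread evenly (assumption): 1 − 0.85/4 = 79% (5 weeks) or 1 − 0.62/4 = 84.5% (6 weeks). Hence most such scans miss the cut, but not all.

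**3. The plan's own figure (14.1.1): 184 events.** Assume exponential DFS of 74% and 82% at 3 years, uniform accrual over 3 years and follow-up of 3 to 6 years. Then P(event) = 1 − (S3 − S3²)/(−ln S3), where S3 is 3-year DFS.
- Control: 1 − (0.74 − 0.5476)/0.3011 = 0.361; × 211 = 76.2.
- Intervention: 1 − (0.82 − 0.6724)/0.1985 = 0.256; × 422 = 108.1.
- Total 184.3, so 184 is reproduced.
- A strict 3-year cut would give 211 × 0.26 + 422 × 0.18 = 131 events. The sizing therefore counts events after 3 years.

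**4. Size under a fixed 3-year comparison.** Assume a constant hazard and 6 weeks of CRT. The previous deferral scan is also late, at 24 + 1.38 = 25.4 months, and the 2.5-year visit falls at 31.4 months. Events that could be waiting for the 3-year scan, in points of DFS:

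| Curve | All events since the 2-year scan | Only events since the 2.5-year visit |
|---|---|---|
| 82% | 0.82^(25.38/36) − 0.82 = 4.9 | 0.82^(31.38/36) − 0.82 = 2.1 |
| 74% | 0.74^(25.38/36) − 0.74 = 6.9 | 0.74^(31.38/36) − 0.74 = 2.9 |

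Multiply by the share of scans after the cut (0.845) and by the share of the intervention arm that defers. The documents do not give that share, so it is assumed.
- 82% curve, 20% to 70% defer: 0.20 × 2.1 × 0.845 = 0.4 to 0.70 × 4.9 × 0.845 = 2.9 points.
- 74% curve, 30% to 50% defer: 0.30 × 2.9 × 0.845 = 0.7 to 0.50 × 6.9 × 0.845 = 2.9 points.

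Taking CRT as 5 weeks moves these by less than 0.2 points.

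**5. If operated scans scatter too.** Give operated patients the same even ± 2 months around 36 (assumption), and treat the pool of waiting events as equal in both pathways. Half of their scans also miss the cut, so the excess is 0.845 − 0.50 = 0.345. The same inputs then give 0.20 × 2.1 × 0.345 = 0.1 to 0.70 × 4.9 × 0.345 = 1.2 points (82% curve), or 0.3 to 1.2 (74% curve).

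**6. Registration origin (3.1).** Registration up to 4 weeks (0.9 months) before CRT puts the operated check at 36.0 to 36.9 months and the nominal deferral scan at 37.1 to 38.3 months. The gap between pathways stays, but both checks can then fall after the cut.

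**The case against.** The strongest reply is that little is fixed here. The primary endpoint of this trial is recruitment. The phase III endpoint comes by substantial amendment, and the pooled analysis is left to the phase III protocol. The 184-event sizing points to a time-to-event analysis, in which a recurrence found at 37 months still counts. End of CRT is the protocol's usual clock for operated patients too, so the sentence in 11.1 may simply be out of line, and sites that schedule by the form would align the pathways. Deferral patients also have CEA at 2.5 years, and a rising CEA leads to CT (section 11).

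Most of this stands as a limit on size. It does not remove the conflict, which lies in rules as stated and not in details left to an SAP. Feasibility patients will be scanned and dated under these rules before any phase III text exists.

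A reader might infer that every recurrence found at the deferral patients' 3-year scan is lost from phase III DFS, or that the bias is the same whichever origin is used. The documents support neither. The window lets about 16% to 21% of those scans fall by 36 months (even spread assumed), the sized design counts later events, and a registration origin weakens the contrast.

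**Conclusion.** The protocol gives two origins for phase III DFS (registration, start of CRT) and two anchors for the 3-year disease check (start of CRT, end of CRT). As written, the deferral scan follows the operated patients' check by a nominal 1.1 to 1.4 months.

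Under a fixed 3-year comparison, as 4.5 and 11.1 word it, this favours the intervention arm by roughly 0.4 to 3 points against a planned difference of 8 (74% to 82%). With operated scans scattered around 36 months it is about 0.1 to 1.2 points. These figures rest on assumptions the documents do not settle: the share of patients deferring, the share of recurrences first found at that scan, a constant hazard and the spread of visits. They also treat all DFS events as scan-dated, which deaths are not, so they lean high.

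In a time-to-event analysis of the 184-event design, the effect is a detection delay of 1.1 to 1.4 months and not a lost event. The conflict should be corrected, but it does not invalidate the design.

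**What to change.** Reconcile sections 3.1, 11.1, 11.2.1 and 11.3 and the annual forms (8.1, 8.3, 10, 10.1, 10.3) so that there is:
- one time origin for DFS;
- one anchor and one window for the 3-year disease check in all three pathways.

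Which schedule to keep is for the investigators; what matters statistically is that it is the same for all patients. If a 3-year DFS proportion is reported, read it after that common window has closed for everyone. Assigning recurrences found at a scheduled visit to the nominal visit time is an option that can be left to the SAP.

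The cost is wording only, with no extra scan. The substantial amendment already planned to add the phase III endpoint could carry it.

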## 11.2 DEFERRAL OF SURGERY FOLLOW-UP

Patients are reviewed in clinic at regular intervals for 5 years. Clinical assessment includes a digital rectal examination (DRE) with a blood test for CEA at each clinic visit. Patients will have an MRI scan approximately mid-way through chemotherapy treatment once they have received their first 12 weeks of therapy.

After completion of chemotherapy, patients will be reviewed every 3 months until 2 years from the completion of CRT and then every 6 months for a further 3 years. The full details of the timings of out-patient clinics, MRI, CT and flexible Sigmoidoscopy/Colonoscopy are included in the table in Section 11.2.1 below. Colonoscopies are recommended as per NICE guidance for colorectal follow-up. Disease status for the assessment of overall survival and disease free survival will be collected at 10 years using the surgical clinics/GP patient records

The timing, indication and **interpretation of biopsies** are critically important in the context of this trial. The details for preparing the biopsy specimen and histopathological analysis are included in the Histopathology protocol in [Appendix 5](#). Blind biopsies are discouraged, i.e. if there is no abnormality on sigmoidoscopy/colonoscopy, then we do not recommend biopsies directed at the mucosa once occupied by the tumour. Biopsies are discouraged unless: i) an area of residual disease is visualised at (and no earlier than) 6-month Sigmoidoscopy; ii) a clinically suspicious area develops/re-appears at Sigmoidoscopy/colonoscopy; iii) MR changes raise the suspicion of re-growth or relapse.

Patients with evidence of clinical or radiological local re-growth or pelvic relapse will be referred immediately to the surgical team for urgent biopsy. Radiological, Endoscopic or Clinical changes that suggest a clinically suspicion of re-growth or pelvic relapse require urgent discussion at a colorectal MDT. If not yet performed an urgent up-to-date MRI (< 1 month) is required. If urgent salvage surgery is recommended, a PET/CT scan will be performed routinely pre-operatively to out rule occult metastatic disease as recommended by National guidelines.

Subjects with metastatic disease detected during follow-up will be treated according to the local MDT recommendation. If the MDT decides that palliative care is required, the patient will discontinue trial treatment and be classed as 'end of study' but still followed up (by completion of the **ANNUAL FOLLOW-UP Form**), with analysis for the primary endpoint assessed on an intention to treat basis.

**Patients with evidence of clinical or radiological local re-growth or pelvic relapse must be treated at least as urgently as a primary rectal cancer by the surgical team. Refer to deferral of surgery and regrowth pathways in Section 8.**

After surgery patients will receive the post-surgery follow-up as described in Section 11.1 above.

### 11.2.1 SURVEILLANCE SCHEDULE FOR PATIENTS WHO DEFER SURGERY

| Time line from end of CRT     | Visit window | Clinic out-patient appointment b | Patient reported outcome measures c | Scans     | Endoscopy   | Completion of Case Report Forms d                                                                              |
|-------------------------------|--------------|---------------------------------------------|------------------------------------------------|-----------|-------------|---------------------------------------------------------------------------------------------------------------------------|
| 6 months ae        | ± 1 month    | X                                           |                                                | MRI       | Flex Sig    | 5B.INTERVENTION ARM POST-TREATMENT MRI
12. SURVEILLANCE                                                                |
| 9 months e         | ± 1 month    | X                                           |                                                | MRI       | Flex Sig    | 5B.INTERVENTION ARM POST-TREATMENT MRI
12. SURVEILLANCE                                                                |
| 1 year e           | ± 1 month    | X                                           | EORTC QLQ-C30, LARS, EQ-5D                     | MRI
CT | Colonoscopy | 5B.INTERVENTION ARM POST-TREATMENT MRI
10. TOXICITY
11. ANNUAL FOLLOW-UP
12. SURVEILLANCE
17. QUALITY OF LIFE |
| 1 year 3 months               | ± 1 month    | X                                           |                                                |           |             | 12. SURVEILLANCE                                                                                                          |
| 1 year 6 months e  | ± 1 month    | X                                           |                                                | MRI       | Flex Sig    | 5B.INTERVENTION ARM POST-TREATMENT MRI
12. SURVEILLANCE                                                                |
| 1 year 9 months               | ± 1 month    | X                                           |                                                |           |             | 12. SURVEILLANCE                                                                                                          |
| 2 years e          | ± 1 month    | X                                           |                                                | MRI
CT | Flex Sig    | 5B.INTERVENTION ARM POST-TREATMENT MRI
11. ANNUAL FOLLOW-UP
12. SURVEILLANCE                                        |
| 2 years 6 months e | ± 1 month    | X                                           |                                                |           |             | 12. SURVEILLANCE                                                                                                          |
| 3 years e          | ± 2 months   | X                                           | EORTC QLQ-C30, LARS, EQ-5D                     | MRI
CT | Flex Sig    | 5B.INTERVENTION ARM POST-TREATMENT MRI
11. ANNUAL FOLLOW-UP
12.SURVEILLANCE
17. QUALITY OF LIFE                  |
| 3 years 6 months              | ± 2 months   | X                                           |                                                |           |             | 12. SURVEILLANCE                                                                                                          |
| 4 years e          | ± 2 months   | X                                           |                                                | MRI       | Flex Sig    | 5B.INTERVENTION ARM POST-TREATMENT MRI
11. ANNUAL FOLLOW-UP
12. SURVEILLANCE                                        |
| 4 years 6 months              | ± 2 months   | X                                           |                                                |           |             | 12. SURVEILLANCE                                                                                                          |
| 5 years e          | ± 3 months   | X                                           | EORTC QLQ-C30, LARS, EQ-5D                     | MRI       | Colonoscopy | 5B.INTERVENTION ARM POST-TREATMENT MRI
11. ANNUAL FOLLOW-UP
12. SURVEILLANCE
17. QUALITY OF LIFE                 |

a This visit should take place once the patient has completed chemotherapy. It is recommended that a CT scan is also performed following the completion of chemotherapy as is usual practice.

b Each clinic out-patient appointment should include a digital rectal exam and CEA (tumour marker) blood test.

c EORTC QLQ-C30, LARS & EQ-5D are included in the QUALITY OF LIFE CRF.

EORTC QLQ-C30, European Organisation for Research and Treatment of Cancer Quality of Life questionnaire v3.

LARS, Low Anterior Resection Syndrome Score. EQ-5D, EuroQol Group EQ-5D Health Questionnaire.

d A SURVEILLANCE Form should be completed at the time of a confirmed or equivocal diagnosis of regrowth. If a patient has an unsalvageable regrowth (see definition in Section 11.3) then this should be recorded on the ADVERSE EVENT Form in addition to the SURVEILLANCE Form.

e If patient has consented to the additional blood sample collection for research (Section 10.4, circulating tumour DNA and markers of cell proliferation and apoptosis) then these samples should be collected during the clinic out-patient appointment, ideally at the same time as the routine blood tests are performed.

Flex sig: flexible sigmoidoscopy.

